#### Interim analyses {21b}

No interim analyses are planned for this trial.

#### Methods for additional analyses (e.g., subgroup analyses) {20b}

Although not formally powered to examine sex differences, results will be reported separately for men and women to enhance transparency and inform data interpretation.

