### Sample size {14}

An a priori power calculation was performed for the primary outcome (weight) using nQuery 7.0 (Statistical Solutions Ltd, Cork, Ireland). In our power analyses, we made the following assumptions: (1) power ≥ 0.90 and above for the primary outcome is ideal; (2) the significance level under the null hypothesis will be set at *α* = 0.05; (3) null hypotheses will be tested against two-directional (that is, two-tailed) alternative hypotheses; (4) a 3-kg between-group difference in weight loss was deemed the minimum difference of clinical importance; and (5) the primary analysis will use the intent-to-treat principle in which all randomized participants are analyzed. We will enroll 150 participants (75 participants per randomized group) to provide 90% power at 5% significance to detect a between-group difference of 3 kg in body weight at 52 weeks. With an attrition rate of as high as 20%, we retain 82% power in a sensitivity (completer’s) analysis. Standard deviation (SD) of weight loss used in this calculation was 5.6 kg and was based on a 52-week interventional study using the Colorado Weigh program conducted at our research center [96]. There are no previous data for us to estimate the effect size for any of the outcomes at 52 weeks. If superiority of IMF to DCR cannot be established, we will perform a non-inferiority test using 2.26-kg weight loss as a non-inferiority margin. In this case, we would have 79% power to establish non-inferiority of IMF as compared to DCR assuming no difference in effect of weight loss between the two groups.

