### Assignment of interventions: allocation

#### Sequence generation {16a}

The randomization assignment will be generated by the study biostatistician (ZP) using a computer-generated block randomization performed within strata defined by sex. Stratification by BMI, age, and race/ethnicity is not needed; given the large sample size, randomization alone should produce balance in these factors.

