### Statistical methods

#### Statistical methods for primary and secondary outcomes {20a}

Baseline characteristics will be summarized by treatment groups using descriptive statistics. Normality assumptions will be evaluated, and transformations used (e.g., square root and log) as appropriate. Body weight is the primary outcome variable and others are secondary or exploratory outcomes. Consequently, no adjustment for multiple outcomes will be applied. *P*-values < 0.05 will be considered significant. Any imbalance in baseline characteristics between groups that could potentially be a confounding factor for the outcome will be adjusted for in the statistical model.

The primary analysis will use the “intent-to-treat” principle and all randomized participants will be analyzed. Each continuous outcome will be analyzed using a linear mixed effects model. The fixed effects of the linear mixed effects model will consist of treatment group (IMF or DCR) and time of measurement (i.e., baseline and follow-up time points) and their interaction. Time of measurement will be treated as a continuous or categorical variable, as appropriate. Test of the interaction assesses the difference in post-intervention change from baseline between two groups and is used to quantify the effectiveness of the intervention. The 90% confidence interval for the interaction will be calculated. Incidence of adverse events, protocol modifications, and attrition will be compared between groups using chi square or Fisher’s exact test as appropriate.

To explore the impact of selected biologic, psychosocial, behavioral, and/or environmental variables on the intervention effect, we will initially apply models similar to those being tested in aim 1, with the addition of a potential effect moderator as a covariate and its interaction term (i.e., intervention × moderator × time interaction) in addition to related two-way interaction terms. Among factors with a significant three-level interaction, we will further use post-intervention weight loss as the outcome and multiple linear regression to examine their association with the outcome and its interaction with intervention. Similar multiple logistic regression analysis will also be conducted with the outcome dichotomized as responder and non-responder using clinical criteria.

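### Sex is the stratification factor but is absent from the stated primary model, and the planned results by sex are not tied to an arm-by-sex contrast (two separate, minor points)

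*Protocol article*

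**What the plan says.** **Design.** Sequence generation {16a} describes "computer-generated block randomization performed within strata defined by sex". The same section declines stratification by BMI, age and race/ethnicity, so sex is the only stratification factor named.

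**Primary model.** Under statistical methods {20a}: "The fixed effects of the linear mixed effects model will consist of treatment group (IMF or DCR) and time of measurement", plus their interaction. Sex is not listed. A covariate enters only if a baseline imbalance is found that could confound the outcome.

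**Moderators.** The same section plans an intervention × moderator × time interaction, with the related two-way terms, for selected biologic, psychosocial, behavioral and environmental variables. It does not list them.

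**Sex.** Additional analyses {20b} concedes that the trial is not formally powered for sex differences, then says that "results will be reported separately for men and women to enhance transparency and inform data interpretation". It names no contrast between the sexes and does not refer to the moderator model.

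**Sample size {14}.** Enrolment is set at 150, or 75 in each arm, and this number should "provide 90% power at 5% significance to detect a between-group difference of 3 kg in body weight at 52 weeks". Tests are two-sided, and "Standard deviation (SD) of weight loss used in this calculation was 5.6 kg".

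**The concern.** There are two issues, and they are independent of each other.

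1. **The analysis does not follow the design.** When randomization is stratified by a factor that predicts outcome, a model that omits the factor leaves its variance in the error term and slightly overstates the standard error of the arm effect. The imbalance-triggered covariate rule is unlikely to bring sex in, because stratification is meant to prevent that imbalance. The effect is read from arm × time, as a change from baseline, so the term that matters is sex × time; a sex main effect alone would not be enough.

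2. **Separate results do not answer the question they invite.** If the tables by sex are to help interpret the trial, the quantity needed is the difference between the two arm effects, with its uncertainty. Two results side by side do not supply it. When one sex is the minority, a significant result in one and a non-significant result in the other may reflect subgroup size alone. The plan already contains a suitable model form and does not connect sex to it.

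**Working it through.** **Inputs from the protocol.** 75 per arm, difference 3 kg, SD 5.6 kg, two-sided 0.05 (sample size {14}).

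**Assumptions.** The protocol gives no expected share of women. The three 52-week trials described in its Introduction had 86%, 83% and 56% women, so 56–86% is used as a range. Allocation is 1:1 within each sex, and the SD is 5.6 kg in both.

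**Step 1: reproduce the plan's figures.** SE = 5.6 × √(2/75) = 0.914 kg; 3/0.914 = 3.28; power = Φ(3.28 − 1.96) = 90.7% (noncentral t: 90.3%). The plan states 90%. For completers: "With an attrition rate of as high as 20%, we retain 82% power in a sensitivity" analysis. With 60 per arm the result is 83.5% (noncentral t: 82.9%). Both stated figures are reproduced closely enough.

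**Step 2: sex in the primary model.** Let mean change differ by d kg between the sexes and let f be the share of women. If 5.6 kg is the total SD, the residual SD after adjustment is √(5.6² − d²·f(1−f)).

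| d (kg) | residual SD, f = 0.56 to 0.86 | power, f = 0.56 to 0.86 |
|---|---|---|
| 1 | 5.578 to 5.589 | 90.9% to 90.8% |
| 2 | 5.511 to 5.557 | 91.5% to 91.1% |
| 4 | 5.236 to 5.425 | 93.9% to 92.3% |

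The comparison value is 90.7% unadjusted. The gain is real but small.

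**Step 3: within-sex results under a uniform effect.** Per-arm numbers are 75f women and 75(1−f) men, and power in each sex is from the noncentral t. The sexes are independent, so P(significant in women only) = P_women × (1 − P_men). With a true 3 kg effect in both sexes:

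| Women | Power, women | Power, men | Women only |
|---|---|---|---|
| 56% | 68% | 57% | 29% |
| 70% | 78% | 42% | 45% |
| 75% | 80% | 36% | 52% |
| 83% | 84% | 25% | 63% |
| 86% | 86% | 21% | 67% |

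At 56% women the reverse pattern, significance in men only, has probability 0.573 × (1 − 0.679) = 18%.

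Sensitivity of the women-only figure over the same range of f:
- 20% attrition (60 per arm), 3 kg effect: 30% to 63%.
- Uniform 1.5 kg effect, 75 per arm: 19% to 30%.
- No effect: 0.05 × 0.95 = about 5%, whatever the sex ratio.

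**Step 4: what the contrast would show.** SE of the arm-by-sex difference = 5.6 × √(2/n_women + 2/n_men), per-arm numbers.

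| Women | SE (kg) | 95% half-width (kg) | Power for a 3 kg difference between sexes |
|---|---|---|---|
| 56% | 1.84 | 3.6 | 37% |
| 75% | 2.11 | 4.1 | 30% |
| 83% | 2.43 | 4.8 | 23% |
| 86% | 2.64 | 5.2 | 21% |

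The half-width exceeds the plan's 3 kg minimum important difference throughout. The contrast would not be a powered test. It would hold false claims of a sex difference at 5% and show how little the data can say.

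**The case against.** **The sex section promises reporting, not testing.** It states no within-sex test, hypothesis or decision rule, and it carries a power caveat. This stands: the probabilities in step 3 describe what happens if within-sex results are read at p<0.05, which the plan neither announces nor rules out. The caveat, however, gives no measure of the uncertainty, and the contrast would.

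**The moderator model could already cover sex.** Sex could be one of the selected biologic variables, and a list of moderators may be left to a statistical analysis plan. This also stands, so it would be wrong to say that the plan has no arm-by-sex contrast. What remains is that the section dealing with sex fixes a different form of presentation and does not refer to the interaction model.

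**A reader might infer that leaving sex out of the primary model produces a spurious effect in women only.** It does not. Sex and sex × time terms leave the within-sex arm contrasts unchanged.

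**A reader might also infer that a misleading women-only result is likely.** The documents do not support that. It exceeds one half only with a true effect near 3 kg and about 75% or more women. The plan calls 3 kg the minimum clinically important difference, not the expected effect. The two cited trials reported in kg differed by only 1.6 (6.6 against 5.0) and 1.8 (6.8 against 5.0), in opposite directions.

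**Conclusion.** Both points hold at low severity.

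1. The stated primary model omits the stratification factor. The consequence is a slightly conservative standard error, not bias or an invalid test. The power forgone is at most about 3 percentage points (90.7% against 93.9%) under an assumed sex difference in mean change of up to 4 kg.

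2. Results by sex are planned without being tied to a between-sex contrast. If within-sex results were read at p<0.05, the women-only pattern under a uniform effect would range from about 29% to 67% (3 kg), 19% to 30% (1.5 kg) or about 5% (no effect). These figures rest on the assumed 56–86% women, a common SD of 5.6 kg and 75 per arm. They describe a risk of misreading, not an error that the plan commits.

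The primary comparison of the arms is sound on this point either way.

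**What to change.** - In the primary model, prespecify sex and sex × time as fixed effects because sex is the stratification factor, regardless of any observed imbalance.
- In the section on additional analyses, state that the week-52 arm effects for men and women come from one arm × sex × time model with its lower-order terms, that is, the moderator model already planned, with sex named.
- Report the arm-by-sex difference with its 95% CI, label it exploratory, and state that no claim will be made from within-sex p-values. Keep the existing caveat on power.

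The cost is a few model terms and two sentences. No further data or participants are needed. If the analysis plan already names sex in these roles, a cross-reference is enough.

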#### Methods in analysis to handle protocol non-adherence and any statistical methods to handle missing data {20c}

The primary analysis will use the “intent-to-treat” principle to test our study hypotheses under practical and realistic conditions. All randomized participants will be analyzed. We expect that missingness condition is either missing completely at random (MCAR) or missing at random (MAR). A linear mixed effects model will serve as the primary method to handle missing values. The primary and secondary outcomes will be further examined using various sensitivity analyses including analysis of completers using the above statistical models; imputing missing values using baseline-observation-carried-forward, and then assessing efficacy by analyzing the change score from baseline using two sample *t*-tests or linear regression model while adjusting for other covariates; and finally imputing missing values using Markov chain Monte Carlo multiple imputation to create 20 imputed data sets and then analyzing the data using the linear mixed effects model.

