#### Anthropometric measures

Body weight will be measured using a digital scale in the CU-AMC Anschutz Health and Wellness Center clinic accurate to ±0.1 kg at baseline and at weeks 13, 26, 39, 52, and 78 in the AM, after an overnight fast. Participants will also be given a smart scale (©BodyTrace smart scales (Palo Alto, CA)) for daily home weighing use during the 52-week study intervention. These daily weights will be transmitted via wireless cellular network to a secure website. Height will be measured to the nearest 1 mm with a stadiometer at baseline. Blood pressure will be measured with a manual sphygmomanometer (average of 2 seated values taken after 5 min rest) at baseline and weeks 13, 26, 52, and 78. Waist circumference (cm) will be measured at baseline and weeks 13, 26, 52, and 78 with a tape measure parallel to the floor, just superior to the iliac crest. Fat mass and lean mass will be measured using dual-energy x-ray absorptiometry (DXA) at baseline and weeks 26, 52, and 78.

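### No named missing-data sensitivity analysis lets IMF dropouts alone do worse than MAR, and with similar dropout in the two arms BOCF is anti-conservative as support for the fallback non-inferiority test

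*Protocol article*

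**What the plan says.** The section on non-adherence and missing data ({20c}) expects data to be MCAR or MAR and names the primary approach: "A linear mixed effects model will serve as the primary method to handle missing values". It then lists sensitivity analyses for the primary and secondary outcomes:

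- a completers-only analysis with the same models;
- "imputing missing values using baseline-observation-carried-forward, and then assessing efficacy by analyzing the change score from baseline", by t-test or covariate-adjusted regression;
- "imputing missing values using Markov chain Monte Carlo multiple imputation to create 20 imputed data sets", followed by the mixed model again.

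The sample size section ({14}) adds a second test for the primary outcome: "we will perform a non-inferiority test using 2.26-kg weight loss as a non-inferiority margin", to be done if superiority of IMF is not shown. Section {20c} does not separate the two tests and does not say which sensitivity analyses should support which conclusion. Weight is also recorded at every group class and on home scales; of the latter the article says "These daily weights will be transmitted via wireless cellular network to a secure website".

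**The concern.** For a non-inferiority claim, the missing-data scenario that matters is that IMF participants without a week-52 weight did worse than their observed data predict, while DCR dropouts did not, or did so less. A useful sensitivity analysis moves the IMF arm alone and shows when the claim fails. None of the three named analyses does this.

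- Completers needs an assumption at least as strong as MAR.
- Multiple imputation followed by the same mixed model rests on MAR again, so it should largely repeat the primary result.
- BOCF departs from MAR, but by one rule for both arms. Pulling both arms towards zero change pulls their difference towards zero when dropout is similar. That is normally conservative for superiority and anti-conservative for non-inferiority.

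BOCF also enters the zeros as if they were measured, so the standard error does not reflect the missing information. At stake is a fallback claim of non-inferiority that is wrong but is reported as robust because BOCF agrees with it.

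**Working it through.** **Inputs from the protocol article.** 75 per arm, SD of weight loss 5.6 kg, margin 2.26 kg, attrition up to 20%, non-inferiority power 79% (all {14}); 90% confidence interval ({20a}); 29% and 38% dropout in the DCR and fasting arms of the cited alternate-day fasting trial (Introduction).

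**Assumptions.** Mean DCR loss L of 5 to 7 kg (a cited 52-week trial reports 6.6 kg); true IMF deficit m exactly 2.26 kg; SD 5.6 kg among observed values in both arms; dropout unrelated to outcome unless stated. The protocol does not split attrition by arm, so the splits below are scenarios.

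**The plan's own figure.** SE = 5.6 × √(2/75) = 0.914. Power at true difference 0 = Φ(2.26/0.914 − 1.645) = Φ(0.826) = 79.6% (79.3% with the t distribution), which matches the stated 79%. One-sided 2.5% would give 69.6%. The non-inferiority test is therefore at one-sided 5%, in line with the 90% interval.

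**BOCF formulas.** With dropout dC in DCR and dI in IMF:

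- expected difference D = L(1 − dC) − (L − m)(1 − dI); with equal dropout d this is (1 − d)m;
- variance in an arm with mean loss μ = (1 − d) × 5.6² + d(1 − d)μ²;
- false non-inferiority rate = Φ((2.26 − D)/SE − 1.645).

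**Worked case, 20% in both arms, L = 6.6.**

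- D = 0.8 × 2.26 = 1.81.
- DCR variance = 0.8 × 31.36 + 0.16 × 6.6² = 32.06.
- IMF variance = 25.09 + 0.16 × 4.34² = 28.10.
- SE = √((32.06 + 28.10)/75) = 0.896.
- Rate = Φ(0.505 − 1.645) = 12.7%; simulation of 40,000 trials gave 12.9%.

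This SE is below the 0.914 of complete data, although only 60 per arm are observed. The completers' SE is 5.6 × √(2/60) = 1.02.

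**Results for L = 5 to 7 kg (nominal 5%).**

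| Dropout DCR / IMF | BOCF difference (kg) | BOCF false non-inferiority |
|---|---|---|
| 20% / 20% | 1.81 | about 13% |
| 30% / 30% | 1.58 | 19–21% |
| 29% / 38% | 1.85–2.03 | 8–13% |
| 15% / 25% | 2.20–2.40 | 3.6–5.8% |
| 10% / 30% | 2.58–2.98 | 0.7–2.1% |

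**Where the direction changes.** D exceeds the true deficit when (dI − dC)/dI > 2.26/L, that is above 0.45 at L = 5 and 0.32 at L = 7. For 29%/38% the ratio is 0.09/0.38 = 0.24, so BOCF still understates the deficit. For 10%/30% it is 0.67, so BOCF overstates it.

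**The untested scenario.** Suppose 20% drop out in each arm, the true deficit is 2.26 kg, and IMF dropouts lose 4 kg less than MAR predicts. A MAR analysis, approximated by completers, estimates 2.26 − 0.2 × 4 = 1.46 kg and has a false non-inferiority rate of 19.4%. BOCF estimates 0.8 × 1.46 = 1.17 kg, with about 33% at L = 6.6. The BOCF result would seem to confirm the error.

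**The case against.** Several points on the other side are sound.

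**BOCF does challenge MAR.** A reader might infer that nothing in the list departs from MAR. That is not so: return to baseline is itself a departure, close to the regain that one would fear, and it penalises IMF when IMF loses clearly more participants. With no true difference, 29%/38% dropout creates an apparent IMF deficit of 0.09 × L = 0.45 to 0.63 kg. What is missing is a departure that differs by arm.

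**The direction is conditional.** It depends on dropout by arm and on mean loss, which the protocol does not give. The cited long-term trials had dropout (DCR/fasting) of 29%/29%, 29%/38% and 60%/49%. All three lie on the anti-conservative side of the break-even at 5 to 7 kg, but none is this trial's dropout.

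**The 13% is not the trial's error rate.** A reader might take it so. The mixed model is primary, and under the equal random dropout assumed here it stays near 5%. In simulation at 20% dropout, with completers standing in for the mixed model, completers declared non-inferiority in about 5% of trials, BOCF in about 13%, and both in under 5%. BOCF adds no false primary claims. But it agreed with more than nine in ten of those that occurred, so it is a weak check.

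**Silence is not a plan.** A reader might infer that the home and class weights will be ignored. The article does not specify the imputation model, the list of sensitivity analyses is open, and an analysis plan that is not shown may add to both. Nor does the article say that BOCF must support non-inferiority. Clinic weights at weeks 13, 26 and 39 already inform the mixed model. What stands is the behaviour of the method that is named, applied without distinction between the two tests.

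**Conclusion.** The point holds in a limited form. The three named analyses contain no arm-specific departure from MAR. When dropout is similar, or only modestly higher in IMF, BOCF is anti-conservative as support for the 2.26-kg non-inferiority test: its own false non-inferiority rate is roughly 1.6 to 4 times the nominal 5% in the first three scenarios tabulated (8 to 21%). With a large IMF excess it becomes conservative, and then it can mask true non-inferiority: with no true difference and 15%/25% dropout, its power is about 54% at a 6.6-kg loss. A check whose direction turns on an unknown dropout split is not a dependable one for this test. For superiority, the main objective, shrinkage towards zero is normally conservative and the concern does not apply. The figures rest on the assumed DCR loss, equal SDs, the dropout scenarios and a true deficit exactly at the margin. This is an inexpensive improvement, not a defect in the primary analysis.

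**What to change.** State in {20c}, or in the analysis plan, which sensitivity analyses support which test.

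- **Non-inferiority:** do not cite BOCF as support. Use multiple imputation with a delta-adjusted tipping-point analysis: worsen the imputed week-52 weights of missing IMF participants only, in steps, leave DCR at MAR, and report the delta at which the 2.26-kg conclusion is lost.
- **Superiority:** BOCF may stay. Return-to-baseline multiple imputation makes a similar assumption about the mean and has proper variance.
- **Imputation model:** the home-scale and class weights can serve as auxiliary variables, since they may show the course around dropout and missed clinic visits.

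The cost is some programming and a few lines of text, with no new data collection. The downside is that the robustness statement for a non-inferiority claim may be less favourable.

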#### Plans to give access to the full protocol, participant-level data, and statistical code {31c}

This paper provides the full protocol. Interested individuals should contact the study principal investigator (VC) if interested in other data or documentation of the study.

